#### Inclusion criteria

2.3.1

The inclusion criteria are as follows:

1.oligomenorrhea (menstrual cycle >35 days or <8 cycles per year) with at least one of the following 2 criteria:A.Hyperandrogenism (clinical, biochemical, or both);B.Polycystic ovarian morphologic features (≥12 antral follicles of 2–9 mm diameter in either ovary; an ovarian volume **≥**10 mL in either ovary; or both);2.Age 20 to 40 years;3.Voluntary agreement to participation in the trial and provide informed consent prior to treatment.

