#### Exclusion criteria

2.3.2

We will exclude women who meet any of the following conditions:

1.Pregnancy, labor, or breastfeeding within the past 3 months;2.Intake of oral contraceptives or ovulation-inducing agents within the past 3 months;3.Severe oligomenorrhea with a menstrual cycle lasting >3 months;4.Menstruation lasting >8 days;5.Premature ovarian failure;6.Resistant thyroid disease, Cushing's disease, congenital adrenal hyperplasia, or hyperprolactinemia;7.Ovarian tumors or adrenal tumors that cause hyperandrogenemia;8.Hemorrhagic disease;9.Severe cardiac, pulmonary, hepatic, or renal diseases, central nervous system disorders, or intake of psychoactive drugs;10.Acupuncture treatment within the past 1 month;11.Participation in other clinical trials within the past 3 months;12.Any other conditions considered inappropriate for inclusion in the trial by the investigators.

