#### Primary outcome

2.5.1

The primary outcome is the mean change in menstrual frequency (menstrual cycle/month) from baseline to 16 weeks and 32 weeks (follow-up) after the start of the trial. The menstrual frequency will be assessed to evaluate the improvement in ovulatory functions and restoration of menstruation of PCOS patients.^[19]^ The average menstrual frequency for the last year will be recorded as the baseline evaluation. The average menstrual frequency for 16 weeks during the treatment period will be recorded at a close-out evaluation, and that for another 16 weeks during the follow-up period will be recorded at a follow-up evaluation.

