#### Secondary outcomes

2.5.2

The secondary outcomes include mean changes in menstrual period, levels of estradiol, LH, FSH, and total testosterone, LH/FSH ratio, antral follicle count in the ovary, ovarian volume, BMI, waist-hip ratio (WHR), acne severity, and 36-item short-form health survey (SF-36) scores from baseline to 16 weeks and 32 weeks after the start of the trial.

The menstrual period is defined as the number of days from the first day of the menstrual cycle to the first day of the next menstrual cycle. It is assessed in order to evaluate the restored regular menstrual period.^[16]^ The levels of serum estradiol, serum LH, serum FSH, and total testosterone, and LH/FSH ratio will be estimated to evaluate the participant's sex hormone changes after interventions.^[^2^,^^20^^]^ The morphologic features of polycystic ovaries will be assessed by antral follicle count and ovarian volume via ultrasound imaging. A transvaginal transducer with frequencies of ≥8 MHz detects follicles with diameters in the range of 2 to 9 mm in the ovary and can be used to estimate ovarian volume.^[21]^ Follicular excess and ovarian enlargement are considered accurate markers of polycystic ovarian morphology.^[2]^ The participants’ obesity level will be assessed using BMI and WHR. BMI is defined as the body weight (kg) divided by the square of the height (m^2^). WHR is calculated using the circumference of the waist and hip.^[^22^,^^23^^]^ The acne severity will be assessed using the Pillsbury acne grading system, with grades ranging from 0 to 4. A high-scoring grade indicates more severe acne, that is, grade 0 is considered normal and grade 4 is considered to be severe.^[24]^ We will also assess the quality of life as reflected by an SF-36 score for the participants. The SF-36 questionnaire has been proved to be valid and reliable in each country. It will be used to assess the health-related quality of life of women with PCOS.^[^25^,^^26^^]^ The SF-36 questionnaire is a 36-item, patient-reported survey of patient health consisting of eight subscales, with a total score ranging from 0 to 100. The higher the score, the lesser the disability, that is, a score of 0 is equivalent to maximum disability and that of 100 is equivalent to no disability.^[27]^

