### Statistical methods

2.13

All statistical analyses will be performed using SAS version 9.4 (SAS Institute. Inc., Cary, NC) with a two-tailed test. The level of significance will be set at 5%. Missing data will be substituted using multiple imputations.

The analysis set will consists of a full analysis set (FAS), per-protocol (PP) set, and safety set. The main analyses will be conducted using FAS. A FAS is described as set that is as complete and close as possible to the intention-to-treat. The efficacy test will be assessed by FAS analysis and PP analysis. The safety test will be assessed by intent-to-treat analysis, as well as by PP analysis.

Baseline characteristics of the groups with continuous data will be compared using an independent *t*-test or a Wilcoxon rank-sum test. Baseline characteristics with categorical data will be compared using a Chi-Squared test or Fisher exact test.

The primary outcome measure in this study will be the mean change in menstrual frequency from baseline to 16 and 32 weeks after the start of the trial. To analyze menstrual frequency as the primary outcome, we will perform an analysis of covariance considering the baseline menstrual frequency as the covariate and treatment group as the fixed factor. Additionally, intra-group menstrual frequency changes from baseline to post-treatment will be analyzed using a paired *t*-test or Wilcoxon signed-rank test.

The methods used to analyze the secondary outcome measures will be the same as those used for the primary outcome analyses. If the data type is categorical, it will be analyzed using a Chi-Squared test or Fisher exact test.

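### Week-16 menstrual frequency depends partly on cycle phase at randomisation, and the stated ANCOVA leaves out days since last menses, a nearly free gain in precision

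*Protocol article*

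**What the plan says.** The Primary outcome section sets three windows, all expressed in cycles per month:

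- Baseline: "The average menstrual frequency for the last year will be recorded as the baseline evaluation".
- Treatment: "The average menstrual frequency for 16 weeks during the treatment period will be recorded at a close-out evaluation".
- Follow-up: "that for another 16 weeks during the follow-up period will be recorded at a follow-up evaluation".

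It does not say whether frequency is a count of onsets in the window or is derived from cycle lengths. The Randomization section issues the random number at the second visit and links that visit to no day of the cycle.

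The Statistical methods section names the terms of the ANCOVA: "considering the baseline menstrual frequency as the covariate and treatment group as the fixed factor". Days since last menses appears nowhere in the text shown; Table 1 and Figure 1 are not shown.

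Eligibility bounds the cycle length. Women enter with "menstrual cycle >35 days or <8 cycles per year" and are excluded for "Severe oligomenorrhea with a menstrual cycle lasting >3 months". The Sample size section assumes a difference of 0.14 and an SD of 0.17.

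**The concern.** A 16-week window holds few cycles in these women, so an onset count is small, and whether a woman scores one onset more or fewer depends partly on how long before the window she last bled. Her frequency over the last year measures her rate, not her position in the cycle, so the stated covariate cannot absorb this. The position is known before randomisation and predicts the week-16 outcome. Leaving it out keeps explainable variance in the treatment comparison, which matters in a trial of about 25 to 30 women per arm. A pilot meant to inform a full-scale trial also gains from a cleaner variance estimate.

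**Working it through.** **Inputs from the protocol article.** Window 112 days; eligible cycles from about 35 days to about 3 months; difference 0.14 and SD 0.17; two-sided 5% level, 80% power; 25 per arm, 60 women with 15% dropout.

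**Inputs assumed.** Frequency is onsets per calendar month of 30.44 days. The window starts at or close to randomisation. The 0.17 is the SD of the change. Within-woman CV of cycle length ranges from 0 to 0.5.

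**1. The plan's own figure.** Normal formula: 2 × (1.96 + 0.84)² × (0.17/0.14)² gives 24 per arm. The t-based calculation gives 25, with power 81.4%. Dropout: 25/0.85 = 29.4, so 30 per arm and 60 in total. The stated size reproduces.

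**2. Size of the count.** 112/30.44 = 3.68 months, so one onset is 1/3.68 = 0.272 per month (0.25 with a 28-day month). Expected onsets run from 112/90 = 1.2 to 112/35 = 3.2.

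**3. Illustration.** Take a woman with regular 60-day cycles.
- If she last bled 55 days before the window, she bleeds on days 5 and 65: two onsets, 0.54 per month.
- If she last bled 5 days before, she bleeds on day 55 only (the next is day 115): one onset, 0.27 per month.

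Only women who bled fewer than 8 days before the window get the lower score, which is 8/60 = 13% of entry days at this cycle length.

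**4. Upper bound with perfectly regular cycles.** The phase variance of the count is f(1 − f), where f is the fractional part of 112/cycle length. Its maximum is 0.25, so the SD is 0.5 × 0.272 = 0.136 per month. Its average over f is 1/6, so the SD is 0.408 × 0.272 = 0.111.

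**5. Irregular cycles, by simulation.** There were 60,000 women per scenario, with gamma-distributed cycles (18-day minimum), a random entry day, no treatment effect and accurate 12-month counts. Woman-level mean cycle length was either uniform on 35–90 days or normal (mean 55, SD 12) clipped to that range. The table gives the share of ANCOVA residual variance, after baseline frequency, removed by a linear term for days since last menses (uniform / normal).

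| CV | SD of week-16 change | Share, week 16 | Share, week 32 |
|---|---|---|---|
| 0 | 0.137 / 0.128 | 61% / 54% | 0.8% / 4.0% |
| 0.1 | 0.143 / 0.137 | 50% / 46% | 0.9% / 2.6% |
| 0.2 | 0.159 / 0.159 | 31% / 29% | 1.0% / 1.1% |
| 0.25 | 0.170 / 0.173 | 23% / 22% | 0.8% / 0.9% |
| 0.3 | 0.183 / 0.188 | 16% / 15% | 0.8% / 0.5% |
| 0.4 | 0.214 / 0.221 | 8% / 8% | 0.3% / 0.1% |
| 0.5 | 0.246 / 0.255 | 5% / 4% | 0.2% / 0.1% |

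The CV that matches the protocol's SD of 0.17 is about 0.25. Adding quadratic and interaction terms there raises the share only to 24–26%, so a linear term is enough.

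**6. What the gain is worth.** With a 22% reduction, 0.17 × √0.78 = 0.150. By the normal formula, n per arm for 80% power falls from 24 to 19, and power at 25 per arm rises from 83% to 91%. In patients, 1/0.78 = 1.28, or roughly 30% more women.

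**7. How far chance imbalance could move the estimate.** At CV 0.25 (uniform) the residual SD after baseline is 0.166, so the phase component is 0.166 × √0.228 = 0.079. With 25 per arm its standard error on the arm difference is 0.079 × √(2/25) = 0.022. Two standard errors are about 0.045, roughly a third of 0.14.

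**The case against.** The case against is strong on size. The within-woman CV is in neither the protocol article nor any other document at hand, and a gain near one half needs nearly regular cycles, a demanding assumption in oligomenorrhea. ANCOVA on the baseline value is a standard choice, and further covariates are often settled in the analysis plan, which is not shown. If frequency is derived from completed cycle lengths, the mechanism changes. The assumed SD comes from a study with the same outcome, so it may already contain this noise. All of this stands and limits the point, but does not remove it: the article names the model's terms, and a better model is available at almost no cost.

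A reader might infer several stronger things that the documents do not support:

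- **Phase drives most of the noise, or noise as large as the assumed SD.** At the protocol's own SD the share is under a quarter, and the component is about 0.08 against 0.17.
- **Phase imbalance could create or hide a difference of 0.14.** That is 0.14/0.022 = 6.4 standard errors. Even at the regular-cycle maximum, 0.136 × √(2/25) = 0.038 and 0.14 is 3.6 standard errors.
- **The 0.27 step makes 0.14 unreachable.** Group means are not confined to one woman's step, and the covariate would not remove the step in any case.
- **The comparison is biased.** Randomisation balances phase in expectation.

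**Conclusion.** The point holds as a moderate loss of precision at week 16. If frequency is an onset count, the stated ANCOVA omits a valid pre-randomisation predictor worth about 23% of residual variance at the CV of about 0.25 that matches the protocol's SD, with a range from about 50% at CV 0.1 to about 4% at CV 0.5. For the 32-week comparison the share is about 1% at CVs of 0.2 to 0.3 and no more than 4% in any scenario run, so nothing is asked for there. No bias, inflation of type I error or sample size error is shown. The figures rest on the onset count, a window starting near randomisation, accurate recall of the last year, no treatment effect on cycle length, and a CV that must be assumed.

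**What to change.** Pre-specify, before any outcome data are seen, days from the first day of the last menses to randomisation as a second baseline covariate, entered linearly, in the week-16 ANCOVA of menstrual frequency only. Leave the week-32 model as it is. In particular, do not adjust week 32 for days since last menses at week 16, because treatment can change that value and adjusting for it could remove part of the effect. If the full protocol derives frequency from cycle lengths, rework the expected gain before adopting the covariate.

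The cost is one degree of freedom (with 50 women, residual degrees of freedom fall from 47 to 46) and at most one extra date on the case report form. The secondary outcome of menstrual period, defined as "the number of days from the first day of the menstrual cycle to the first day of the next menstrual cycle", already needs onset dates. The downside is that the gain shrinks if cycles are very irregular.

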The participants in the control (usual care) group will be managed with the usual care regimen only. They will receive health advice and lifestyle management brochures regarding diet along with regular meals, sufficient sleep, and appropriate exercise once a month for 16 weeks.

The participants are not permitted concomitant medication like OCPs or ovulation induction that may affect menstrual cycles. And, acupuncture, moxibustion, cupping, and other traditional Chinese/Korean medicine treatments are neither allowed if they are judged to affect the outcome measures.

Adherence to acupuncture will be checked every 4 weeks during the treatment period, and participants who have an adherence rate of less than 70% will be dropped out.

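### Menstrual frequency is averaged over fixed 16-week windows, so on a literal reading the weeks after a conception count as weeks without menses, against the outcome's stated purpose

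*Protocol article*

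**What the plan says.** Section 2.5.1 makes the primary outcome the change in menstrual frequency, in cycles per month, from a baseline averaged over the previous year. For the treatment period: "The average menstrual frequency for 16 weeks during the treatment period will be recorded at a close-out evaluation". For follow-up: "that for another 16 weeks during the follow-up period will be recorded at a follow-up evaluation". Both windows are fixed lengths of calendar time. The same section gives the purpose: "The menstrual frequency will be assessed to evaluate the improvement in ovulatory functions and restoration of menstruation of PCOS patients".

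Three other statements bear on who can conceive during the trial:

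- Inclusion (2.3.1): "Age 20 to 40 years".
- Exclusion (2.3.2) deals with pregnancy at entry: "Pregnancy, labor, or breastfeeding within the past 3 months".
- Interventions (2.4): "The participants are not permitted concomitant medication like OCPs or ovulation induction that may affect menstrual cycles".

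Statistical methods (2.13) makes the full analysis set (FAS) the main analysis set, with analysis of covariance adjusted for baseline frequency, and adds: "Missing data will be substituted using multiple imputations". The article does not say how weeks after a conception enter the frequency.

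**The concern.** The denominator is calendar time, not time during which a woman could menstruate. Conception shows that ovulation took place, and it also stops menses. Under a literal count, a woman in whom the intended effect occurred and who conceived moves down the scale, and can reach zero in the follow-up window. For her, the score runs opposite to what the outcome is meant to measure.

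Conception is foreseeable: the women are 20 to 40 years old, pregnancy is an exclusion only at entry in the text shown, and oral contraceptives are barred. The introduction links PCOS to anovulatory infertility. Under the trial's hypothesis, any imbalance would be expected to favour the acupuncture arm.

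With about 25 evaluable women per arm, one or two such values can move both the estimated difference and the SD. The article says the results are to inform a full-scale trial, so a distorted effect or SD would carry into its planning.

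**Working it through.** **Inputs from the article (2.8, 2.13).** Difference 0.14, SD 0.17, two-sided 5%, 80% power, 25 per arm, 60 randomised after 15% dropout.

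**The plan's own figure.** d = 0.14/0.17 = 0.82. The normal formula gives 24 per arm, the t-test 24.1, rounded up to 25. With d rounded to 0.8, the normal formula gives 25. Dropout: 25/0.85 = 29.4, so 30 per arm and 60 in total. The stated size reproduces. Power at 25 per arm is 81.4% (t-test).

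**Scale.** Sixteen weeks is 112 days, or 112/30.44 = 3.68 months. One menses is therefore worth 1/3.68 = 0.27 cycles/month, and the assumed effect of 0.14 is about half a menses per woman per window.

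**Assumptions not in the article.** Control mean 0.50 to 0.70 cycles/month, acupuncture 0.14 higher; the number of conceptions; post-conception weeks counted as without menses; an unadjusted t-test in place of the planned analysis of covariance.

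**One or two conceptions in a given window.** A woman with expected frequency f who conceives at a uniform time in the window loses f/2 on average. One who is pregnant throughout loses f. With k such women among 25, the arm mean falls by k·f/50 or k·f/25. For one acupuncture conception:

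- Uniform time, f = 0.84: 0.14 − 0.84/50 = 0.123. With f = 0.64: 0.14 − 0.64/50 = 0.127.
- Whole window, f = 0.84: 0.14 − 0.84/25 = 0.106. With f = 0.64: 0.14 − 0.64/25 = 0.114.

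Power by simulation (at least 20,000 replicates per setting), over control means 0.50 to 0.70:

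| Conceptions, acupuncture vs control | Uniform time (treatment window) | Whole window (follow-up) |
|---|---|---|
| 0 vs 0 | 81% | 81% |
| 1 vs 0 | 65–71% | 41–55% |
| 2 vs 0 | 48–59% | 9–26% |
| 1 vs 1 | not tabulated | 54–66% |

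In the last row the difference hardly moves: with means 0.84 and 0.70 it is 0.14 − (0.84 − 0.70)/25 = 0.134. The loss of power comes from the added variance.

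**The same in terms of conception rates.** Let p_t and p_c be the proportions conceiving during weeks 0–16, at a uniform time, with no new conceptions later. Let f_t = f_c + 0.14.

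- 16 weeks: difference = f_t(1 − p_t/2) − f_c(1 − p_c/2); variance per arm = 0.17² + p·f²/3 − (p·f/2)².
- 32 weeks: difference = f_t(1 − p_t) − f_c(1 − p_c); variance per arm = 0.17²(1 − p) + p(1 − p)f².

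Example, f_c = 0.50, 10% vs 5%: at 16 weeks 0.64 × 0.95 − 0.50 × 0.975 = 0.120; at 32 weeks 0.64 × 0.90 − 0.50 × 0.95 = 0.101.

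| p_t vs p_c | 16-week difference (power) | 32-week difference (power) |
|---|---|---|
| 5% vs 5% | 0.136–0.137 (69–73%) | 0.133 (52–60%) |
| 10% vs 5% | 0.117–0.120 (51–58%) | 0.094–0.101 (25–34%) |
| 20% vs 5% | 0.077–0.089 (22–32%) | 0.015–0.037 (5–8%) |

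Ranges cover f_c = 0.65 and 0.50. The shift is larger at 32 weeks because a woman who conceived during treatment contributes no menses to follow-up.

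**The case against.** A reader might infer that the plan scores a woman who conceives as a treatment failure. It does not. The outcome is continuous, there is no failure category, and the article does not state how pregnancy is handled. Setting her later data to missing and imputing them under 2.13 also fits the text, and the loss calculated above would then not arise in that form. Imputation would, however, fill in menses that she could not have had, and would do so by default rather than by a chosen strategy.

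A reader might also infer that bias against acupuncture is established. It needs two conditions: that the weeks are counted, and that conceptions are unequal. The article gives no conception rate, does not require a wish to conceive, and bars oral contraceptives but not other contraception. Its own citations are mixed. The discussion cites a review with no clinically relevant difference in clinical pregnancy rate against sham; the introduction cites low-level evidence of benefit on pregnancy rates when acupuncture is added to medication.

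The article condenses a fuller protocol, and Figure 1 and Table 1 are not shown. The absence of a pregnancy-withdrawal rule is therefore no finding. The study is also a pilot on feasibility, so lost power matters less than it would in a confirmatory trial.

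What remains is a rule that the article does state: averaging over fixed windows, for an outcome meant to reflect ovulation. Applied literally in the FAS, it counts pregnancy amenorrhoea as absent menses.

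**Conclusion.** The point holds in conditional form. The fixed-window definition, read literally, gives a low frequency to a woman who conceived after ovulation returned. More conceptions under acupuncture would pull the estimate towards zero, mostly at 32 weeks. Equal rates would leave the mean difference nearly unchanged and raise the variance.

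The size cannot be fixed from the article. The power of 65–71% for one acupuncture conception belongs to the treatment window, and 41–55% to a pregnancy lasting the whole follow-up window. The whole-window figures should not be read as the treatment-window effect, since pregnancy is excluded at entry and a full window without menses would need conception at about its start. All these figures rest on the assumed means, the assumed number of conceptions and an unadjusted comparison. They show that one or two women matter at this sample size; they do not predict the trial's result.

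**What to change.** In 2.5.1, and in the analysis plan:

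1. State that weeks after estimated conception are not counted as amenorrhoea, and that frequency in the window of conception is the number of menses divided by the time up to conception.
2. Name pregnancy as an intercurrent event, with a stated strategy for a woman with little or no time at risk in a window. Dividing by time at risk is not enough: a woman who conceives before her first menses in the window still scores zero, and one who conceives during treatment has 0/0 in follow-up. Leaving her out would remove her from the FAS because of her outcome. Either a favourable value or imputation under an explicit hypothetical strategy would keep her in.
3. Add one sensitivity analysis that counts conception as favourable, and report pregnancies by arm.

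The cost is a few sentences, with no change to treatment, visits or sample size. The downsides are less precise frequencies for the few women affected, and a choice of strategy for the follow-up window that must be made and justified before the data are seen.
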